**Eligibility criteria {10}**

Eligibility inclusion criteria for participation are:

1. Be engaged in commercial or transactional sex in Yaoundé, Cameroon
2. In receipt of a recruitment coupon (given by RDS)
3. Aged over the age of 15
4. Not married
5. Identify as woman
6. Have at least one economic dependent living in Yaoundé
7. Have their own, password protected, phone and be able to respond to SMS messages
8. Be HIV negative at enrolment

Eligibility exclusion criteria for participation are:

1. Those under 21 years old who cannot obtain parenteral or guardian consent to participate in the study

**Who will take informed consent? {26a}**

Trained enumerators take informed consent by reading and explaining the information sheets (containing information on the study, objectives of the research, risks and benefits and explaining that participation is voluntary) to potential participants. Participants then have the opportunity to have an informed discussion with the enumerators regarding the study. Participants 21 years old and over are considered majors, and those under the age of 21 are minors. Majors can offer their own consent to participate in the study. For minors, an adult representative/guardian must undergo a similar informed consent, receiving the same information as the participant, before the assent from the minor in a separate room. Participants are never referred to as girls or women who engage in commercial or transactional sex to the adult representative, to minimise adverse consequences. If an adult representative does not offer their consent, a minor cannot participate. If consent is offered, a trained enumerator will then take a minor through an informed assent process, following the same steps as that for a major. Adult representatives offering consent and all participants (minor and major) will receive a hard copy of the consent. An electronic copy, for researchers, of all consent forms (adult representative, minor, major) is stored electronically using an ODK-based survey.

**Additional consent provisions for collection and use of participant data and biological specimens {26b}**

Participants are informed during the informed consenting process that they will undergo biological tests at three different points in the study. HIV and STIs will be tested at these three points, and they will also receive testing for other bacteria and fungi in the vagina to understand their non-sexually transmitted infection status during the final testing for the study. It is explained to participants that the reason we collect their data and biological specimens is to meet the research objective. Consent for biological specimens required for infection testing, using vaginal swabs and blood tests, is obtained during the consenting process.

**Patient and public involvement**

The partner CBOs who maintain a close relationship with the target population were consulted throughout the design phase of the intervention and the study. Formative interviews and focus groups with girls and women engaging in commercial and transactional sex were also conducted to ensure the appropriateness of language employed in the survey, willingness to participate in the study and willingness to accept the intervention. A key concern was that participants would be unwilling to accept the results of the randomisation process. We sought feedback during formative interviews and focus groups on the randomisation design by presenting potential participants with alternative randomisation designs e.g., computer randomisation, public randomisation, and private randomisation. The chosen design was a private participatory draw as this was described as the fairest and most transparent design. We asked participants to support the recruitment of participants in the study using RDS, a chain referral sampling method. Participants were asked to invite up to three of their peers to participate in the study. Once the analysis of the data is complete, participants and the general public will be invited to a dissemination workshop where the results will be presented.

**Interventions**

**The explanation for the choice of comparators {6b}**

The trial will compare participants who receive a free health insurance product with participants who receive nothing. It is expected that there will be equal proportions for the control and treatment groups and that the two groups (treatment and control) will be similar as they are taken from the same population (girls and women engaging in commercial and transactional sex).

**Intervention description {11a}**

The insurance product, provided by GMC Insurance, covers the participant and up to six of their (nominated) economic dependents and is offered for 12 months. An economic dependent is anyone that depends on the participant financially for health care and can include family members, friends and sex work intermediaries (e.g., pimp). The health insurance product provides free health coverage, there are no out-of-pocket costs, with a cumulative ceiling for each group (the participant and their economic dependents) of 500 000 FCFA (= 638,55 GBP, in 2022 prices) following an illness or an accident and is only valid at the Cité Verte Hospital, Yaoundé, Cameroon. The negotiated ceiling of 500 000 FCFA provides good coverage of health expenses for 12 months in Cameroon. If the sum of 500,000 FCFA has been reached (by the participant and their economic dependents combined), participants must pay for the health expenses themselves. Before the group reaches the 500 000 FCFA limit, the participant will be notified to ensure that they are informed when consuming health care. Costs covered by the insurance product are: consultation fees; pharmaceutical fees; medical fees and; hospitalization fees for non-chronic pathologies. Costs not covered by the insurance product are: chronic diseases (e.g. diabetes, high blood pressure, asthma, sickle cell anaemia, obesity...); maternal health care (prenatal care, delivery, postnatal care); illness resulting from civil or foreign war, civil commotion or riot; injury following a violent quarrel except in cases of self-defence; epidemics declared as such by a competent authority (e.g. COVID-19); cosmetic care; dietary care; weight loss or rejuvenation; sterility or abortion treatment; psychiatric treatment; alcoholism; dialysis; dental care and; ophthalmologic care.

The insurance product was rolled out on the 15^th^ of November 2021 and ended on the 14^th^ of November 2022.

Those in receipt of free health care (treatment group participants and their economic dependents) will receive a health insurance pamphlet (explaining the health insurance product and the terms and conditions of usage) and a health insurance card (see online supplemental file appendix 3). Insured parties seeking free healthcare at Cité Verte Hospital must arrive with their health insurance card and photo identification (ID). The research team will generate IDs which are only valid for the POWER project, for those who do not hold identification.

At the Cité Verte Hospital, those covered by the POWER insurance product are received at a dedicated reception, staffed by an enumerator (who is involved in the administration of the ODK-based survey) and an administrative staff member of the Cité Verte Hospital. Staff at the POWER reception identifies the consumer of free healthcare using the insurance card and photo ID. Eligible patients are then triaged and taken through the Cité Verte Hospital patient care process.

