**Trial design {8}**

This study is a stratified cluster randomised controlled superiority trial with two groups: control and treatment. Private participatory randomisation will be conducted with a target of a 1:1 allocation stratified by the type of risky activity, commercial sex or transactional sex.

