**Recruitment {15}**

Participants are recruited using RDS, a chain-referral recruitment method that allows for unbiased population estimates. Initial participants (seeds) were identified by the CBOs. Seeds, and all subsequent participants, were required to recruit up to three of their friends that met the eligibility criteria. A motivation of 500 FCFA (=0.64 GBP, in 2022 prices) was given to participants for each (up to three) participant recruited. Study staff, alongside peer leaders/mobilisers, will follow participant recruitment, calling participants who have not recruited anyone onto the study to encourage them to do so.

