**Assignment of interventions: allocation**

**Sequence generation {16a}**

Randomisation is conducted at the individual level using a participatory approach with a target of a 1:1 ratio to treatment or control group stratified by engagement in commercial or transactional sex. Formative research, conducted before randomisation, found that participatory randomisation was the preferred method of randomisation by the target population. Participatory randomisation was deemed fairer and more transparent than computer-based randomisation.

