**Statistical methods**

**Statistical methods for primary and secondary outcomes {20a}**

All statistical analyses will be conducted using STATA. Descriptive statistics will first be used to summarise participant characteristics between the study groups. To investigate the effect of health insurance on primary and secondary outcomes, the analysis will use an intention-to-treat (ITT) approach where participants will be analysed in their allocated randomised study group. If there are non-compliers, i.e., participants and economic dependents who do not use the health insurance product when sick, we will also estimate the local average treatment effect (LATE). To investigate the effect of health insurance on primary and secondary outcomes, baseline characteristics will be compared for the treatment and control groups and determine whether there is differential attrition between the two groups. Outcomes for the treatment versus the control group will then be compared accounting for any baseline or attrition differences using ordinary least squared. The analysis will be conducted for all women and then separately for women engaging in transactional and commercial sex separately. A causal mediation analysis will be conducted to assess how much of the effect of health insurance on STI and HIV acquisition operates through risky sexual behaviours.

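### Nothing bars or checks for a control woman being insured as a treated friend's dependent, and the planned LATE would not correct for it

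*Protocol*

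**What the plan says.** Four parts of the protocol bear on this.

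- **Who is insured.** Under Intervention description {11a}, the product "covers the participant and up to six of their (nominated) economic dependents and is offered for 12 months". On nominees: "An economic dependent is anyone that depends on the participant financially for health care and can include family members, friends and sex work intermediaries".
- **How participants are linked.** Under Recruitment {15}, seeds and all later participants "were required to recruit up to three of their friends that met the eligibility criteria".
- **How they are allocated.** Under Sequence generation {16a}: "Randomisation is conducted at the individual level using a participatory approach with a target of a 1:1 ratio". Implementation {16c} describes a separate draw for each woman. Trial design {8} calls the trial cluster randomised, but the described procedure is individual.
- **What is compared.** Under the choice of comparators {6b}: "The trial will compare participants who receive a free health insurance product with participants who receive nothing".

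The non-compliance plan is in Statistical methods {20a}. It identifies non-compliers as "participants and economic dependents who do not use the health insurance product when sick, we will also estimate the local average treatment effect". Section {20c} repeats that non-compliance will be handled by a LATE and adds no definition.

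**The concern.** With 1:1 individual draws, two friends from one referral chain land in opposite arms about half the time. A treated woman may nominate a friend who relies on her for health care costs, and that friend may be a control participant. No section excludes this. Data management {19} screens only for repeat participation. At the hospital, {11a} has staff identify users by card and photo ID, with no stated comparison against the control list.

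A control woman insured this way stays in the control arm under ITT, which is correct, but she no longer receives nothing. The difference between arms then understates the effect of insurance. A LATE could in principle allow for this, but the one described looks only at non-use among insured people and would count her as unexposed. A null result might then be read as insurance failing when part of the control arm had it.

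**Working it through.** **Inputs from the protocol.** Sample size {14} gives 568 control and 579 treated women, a 20% risk of at least one STI, a 6-point reduction (to 14%), 80% power and 5% significance. Two-sided testing is assumed because the protocol does not say. Section {11a} gives up to six dependents per treated woman.

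**Input not in the protocol.** The share *c* of control women covered under a treated woman's policy is assumed to be 5%, 10% or 20%.

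**The plan's own figure.** Power for two proportions with pooled variance under the null is

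Φ[(d − 1.96·SE₀)/SE₁].

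With 20% against 14%:

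- pooled proportion = (568 × 0.20 + 579 × 0.14)/1,147 = 0.1697
- SE₀ = 0.02217 and SE₁ = 0.02213
- power = Φ[(0.06 − 1.96 × 0.02217)/0.02213] = Φ(0.748) = 77.3%

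For 80% power the formula needs 615 per arm. The difference detectable with 80% power at 1,147 women is 6.19 points, which matches the stated 6 only after rounding. That gap is a separate matter. It matters here only because no spare power is left to absorb dilution.

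**Dilution of the ITT.** If each covered control gains the full 6-point benefit, the control risk is 0.20 − 0.06*c* and the difference is 0.06(1 − *c*).

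| Controls covered (assumed) | Women | Share of places | Difference | Power |
|---|---|---|---|---|
| 0% | 0 | 0% | 6.0 points | 77.3% |
| 5% | 28 | 0.8% | 5.7 points | 73.3% |
| 10% | 57 | 1.6% | 5.4 points | 68.9% |
| 20% | 114 | 3.3% | 4.8 points | 59.4% |

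The share of places is *c* × 568/3,474, where 579 × 6 = 3,474 is a ceiling reached only if every treated woman names six people.

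**What the LATE recovers.** Take a true effect of 6 points among users, 70% use in the treated arm and 10% use in the control arm (both rates assumed). The ITT effect is 6 × (0.70 − 0.10) = 3.6 points. The LATE divides this by the difference in exposure between arms:

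- **As the plan describes it**, with control exposure taken as zero: 3.6/0.70 = 5.1 points, still diluted.
- **Use counted in both arms:** 3.6/(0.70 − 0.10) = 6.0 points, the true value.
- **Coverage instead of use**, with all treated women and 10% of controls covered: 3.6/(1.00 − 0.10) = 4.0 points. This drops the adjustment for non-use.

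**The case against.** The strongest reply is that nothing in the protocol shows that any control woman was covered. This stands, and every loss above depends on an assumed rate.

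The nomination rule is also narrower than a list naming friends suggests. A nominee must rely on the treated woman to pay for care, and being her friend in a referral chain does not meet that test. Eligibility {10} requires every participant to have a dependent of her own, so control women enter as providers. This makes overlap less likely but does not exclude it. The secondary outcomes include peers who give financial support and transfers sent and received, so the protocol itself expects money to move within these networks.

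The illustration leans high. A control woman on a friend's policy would not gain cover for her own dependents, and would share one 500,000 FCFA ceiling with the rest of the group. The full 6-point benefit is therefore an upper bound at each assumed rate.

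A reader might also infer that intermediaries, children or relatives are shared between treated and control women. The protocol names these kinds of dependent but nowhere says that they are shared.

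Finally, exposure coding is often left to a statistical analysis plan. That would answer a silent protocol. Here {20a} spells out who the non-compliers are, and the definition covers only insured people.

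**Conclusion.** The point holds as a gap in the plan. The text leaves open a route by which control women could be insured, plans no check for it, and defines non-compliance on one side only. If the route was used, the ITT is biased towards no effect and the LATE as described stays biased the same way.

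On assumed cover of 5% to 20% of controls, the upper-bound loss is 0.3 to 1.2 points of the 6.0-point difference, with power falling from about 77% to between 73% and 59%. These figures assume full follow-up, two-sided testing and the full benefit for each covered control. The LATE arithmetic further assumes that insurance acts only through use and equally in all users.

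The documents do not support the stronger reading that the contrast has in fact been diluted. True overlap may be close to zero, and the check would let the trial say so.

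**What to change.** 1. Before analysis, match the list of insured dependents and cardholders to the control-arm participants. Report how many controls were covered and how many used the cover. Staff who hold the identities can do this before the blinded analysts receive the data.
2. In {20a} and {20c}, define LATE exposure as use of any POWER policy, recorded the same way in both arms. Both non-use in the treated arm and use in the control arm are then counted. Coverage alone should not serve as the exposure, for the reason shown in the working.
3. Keep the ITT as the main analysis.
4. Cover of a control woman's dependents is interference between participants, which the LATE cannot correct. Report it descriptively, and only where the survey identifies those dependents; the protocol does not say that it does.

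Rewording the nomination rule would not help this comparison, because cover ended on 14 November 2022 and this protocol version is dated 10 March 2023.

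The cost is one identity match and a somewhat wider LATE interval. In the example above the denominator falls from 0.70 to 0.60, so the interval widens by a factor of about 0.70/0.60 = 1.17. If no overlap is found, the denominator does not change.

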**Strategies to improve adherence to interventions {11c}**

The main strategies employed to encourage participant adherence to the intervention is to ensure that participants and their economic dependents have the best possible experience whilst accessing care at the hospital and to reduce the barriers to access to care. A key concern is that participants or their nominated economic dependents will not go to the hospital to seek care when sick because they face large barriers to access e.g., lack of understanding of illness, distrust in healthcare or not having enough money to get to the hospital. Treatment participants receive information at randomisation, midline and endline regarding what is provided as part of the health insurance product, how to access it and whom to contact if they are having difficulties. Data is collected during the midline and endline survey regarding the participant's experience of using the health insurance product. If the participant has not used the insurance product because they forgot they are part of the treatment group the participant is reminded of the health insurance product and encouraged to use the intervention if needed by the enumerator and the site supervisor at the end of the survey. If the participant has had a bad experience whilst accessing care at the hospital, this is reported to the site supervisor and to the research staff. This problem will be discussed whilst the participant is being surveyed by the enumerator. At the end of the survey, the site supervisor will discuss their experience with the participant and ensure that any issues will be resolved and encourage them to use their health insurance product if needed. Experienced POWER enumerators are based at the hospital throughout the intervention period to support the patients throughout their clinical pathway. If there are any issues with treatment or access to care, the POWER staff report it directly to the research team for a resolution. The CBOs and specifically peer leaders and mobilisers support the adherence of participants to the intervention by keeping in regular contact with the participants throughout the lifetime of the project. Regular contact allows participants with concerns regarding the project or the intervention specifically the opportunity to speak up. Any problems are communicated to the research team and resolved. All resolutions are discussed with the participants. Peer leaders and mobilisers use their strong relationships with the participants and their status in this vulnerable population to engage participants and encourage adherence to the intervention.

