**Concealment mechanism {16b}**

A protocol has been developed to minimise the opportunity to fix randomisation so participants all receive the treatment. Two balls, one orange (allocating participants to the treatment group) and one white (allocating participants to the control group) are placed in a long black opaque bag. Participants are required to draw one ball out of the bag and cannot see inside. Hence, participant allocation to the treatment and control arm is known by the participants, the enumerators and supervisors at the time of the draw.

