**Data collection and management**

**Plans for assessment and collection of outcomes {18a}**

There are several methods of data collection. The socio-economic and biobehavioural surveys occur over three time periods: baseline, 6 months after baseline (midline), and 12 months after baseline (endline). The surveys are administered in both French and English, depending on the participant's language preference. The primary outcomes of the study are STI acquisition and HIV status will be measured via the biobehavioural and socioeconomic survey conducted at baseline, midline and endline. At baseline, we will test for syphilis, chlamydia, gonorrhoea and trichomoniasis. For financial reasons, we will only collect HIV and the two most prevalent STIs at the midline. At endline we will test for all the STIs tested at baseline (syphilis, chlamydia, gonorrhoea and trichomoniasis). In addition, to allow for a better understanding of the participants' non-sexually transmitted infections status, the levels of GV, Mobiluncus, Candida and streptococcal in the vagina will also be tested. Testing the levels of these bacteria and fungi is a secondary outcome. It is important as sexual activity is associated with an increased risk of imbalance of these bacteria or fungi in the vagina which may lead to infections such as Bacterial vaginosis (BV), Candidiasis and Group B Strep infection. Evidence suggests that there is a positive relationship between a person having these infections and an STI and HIV(17). Biological tests (blood tests and vaginal swabs) to test for STIs, HIV and non-sexually transmitted bacteria and fungi are conducted at the same time as the socioeconomic survey.

Other secondary outcomes are measured via the biobehavioural and socioeconomic survey conducted at baseline, midline and endline. Additional measures for secondary outcomes will also be captured in the fortnightly SMS survey. The survey questionnaire will include sociodemographic questions, income, health status, demand for healthcare, economic shocks, STI prevention, risky sexual behaviours, violence, personality traits and preferences.

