**Data management {19}**

Socioeconomic questionnaires will be administered by enumerators in the field. All potential participants will be screened before recruitment onto the study to ensure they have not already participated. Participant responses are entered directly into an ODK-based questionnaire using Android tablets and uploaded to the ODK secure server in the UK when a 3G/WIFI connection is available (immediately, or at the end of each day). On survey completion, the data will be transferred to the UCL Secure Server, a fully encrypted (SSL) server with a direct data link to the android device. The ODK-based questionnaire is programmed with a logic that minimises missing data (e.g., enumerators will not be able to skip questions) and data quality (e.g., range checks will be conducted regularly). Any issues regarding data quality will be reported to the Principal investigator (PI) and directly to the enumerators and the team in the field.

Biobehavioural survey data will be held on the laboratory registry, which is a confidential registry that does not contain any identifiable personal information. The laboratory registry is paper-based (there are no facilities to have an electronic database) and will be kept securely in a locked cabinet. Paper-based data (laboratory records) will be securely transferred to the JHCP office where they will be transferred to a centralized, 128-bit encrypted and password-protected database. All electronic and encrypted data will be transferred securely to the UCL Secure Server.

Responses, using participant telephones, to the weekly SMS sexual diaries are sent directly to the dedicated server at MTN Cameroon. This server is dedicated to this study and will only contain POWER project data. This server is fully encrypted (SSL) and complies with all international standards and norms in terms of hardware and software security (firewall, antivirus, hubs, VPN). The server is in a data centre in Yaoundé, Cameroon, which is a secure building with fire protection systems, generators, redundant air conditioning, and access security). Only the PI of the study and the director of DINA surveys will have access to the data held on the password-protected server. Data is downloaded and exported to excel weekly and stored immediately on the UCL Secure Server. The data will be deleted from the MTN Cameroon dedicated server for up to three years after data collection, or earlier if requested.

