**Confidentiality {27}**

The following measures have been put in place to ensure data confidentiality and to respect the privacy of participants:

1. Implementation of and compliance with the code of ethics

All study staff, inclusive of hired and trained experienced local enumerators and interviewers, must sign a commitment to comply with the code of ethics. Research partners with access to data (JHCP and DINA surveys) have signed a sub-contract with a clause which ensures that all data collected must remain confidential.

1. Participation is confidential

Socioeconomic and biobehavioural data collection and in-depth interviews and focus groups will be conducted in a private location at the CBOs. Participants must not share a telephone to be enrolled in the SMS survey. They are required to confirm that they have their own, password-protected, telephone and can respond to SMS messages. This is to ensure that only the participant reads and responds to the SMS survey.

1. Secure storage of data

During the trial, all paper-based records will be kept securely in a locked cabinet, in a locked office, and securely transferred to the JHCP office where they will be transferred to a centralized, 128-bit encrypted and password-protected database. All electronic data will be stored on the UCL Secure Server.

1. Aggregation and anonymisation of data

Individual responses will be deidentified and aggregated for analysis and reporting. All published findings, including any quotes used, will not allow for individuals to be identified. All results will be presented in aggregate form.

**Plans for collection, laboratory evaluation and storage of biological specimens for genetic or molecular analysis in this trial/future use {33}**

Once participants have completed the ODK-based socioeconomic survey (0 months, 6 months and 12 months) they will also undergo etiological testing for STIs (chlamydia, gonorrhoea, trichomonas, syphilis) and HIV. Participants will also undergo testing for additional bateria and fungi in the vagina (GV, Mobiluncus, Candida and streptococcal) at endline. Rapid tests are conducted in the CBOs laboratory for chlamydia, gonorrhoea, syphilis and HIV. No rapid test for Trichomoniasis is available in Cameroon, therefore testing will be subcontracted to CRESAR (Centre de Recherche sur la Santé des Armées), a laboratory which has been based in the JHCP premises for over 20 years.

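### Survey enumerators also staff the treatment-only hospital reception, and bad hospital experiences are discussed mid-interview, so interviewer-collected self-reports can differ by arm for reasons other than insurance

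*Protocol*

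**What the plan says.** Three parts of the protocol bear on this.

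- **Hospital staffing.** Intervention description {11a} says that those covered by the insurance are "received at a dedicated reception, staffed by an enumerator (who is involved in the administration of the ODK-based survey"), alongside a hospital administrator. Strategies to improve adherence {11c} adds: "Experienced POWER enumerators are based at the hospital throughout the intervention period to support the patients throughout their clinical pathway".
- **Outcome interviews.** Data management {19} states: "Socioeconomic questionnaires will be administered by enumerators in the field". Section {33} identifies the ODK instrument as the outcome survey: "Once participants have completed the ODK-based socioeconomic survey (0 months, 6 months and 12 months"). Section {18a} confirms its use: "Other secondary outcomes are measured via the biobehavioural and socioeconomic survey conducted at baseline, midline and endline".
- **Content of the interview.** Section {11c} also says: "Data is collected during the midline and endline survey regarding the participant's experience of using the health insurance product". Of a bad experience at the hospital it says: "This problem will be discussed whilst the participant is being surveyed by the enumerator". The same section places reminders, and resolution by the site supervisor, at the end of the survey.

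On masking, section {16b} notes that "participant allocation to the treatment and control arm is known by the participants, the enumerators and supervisors at the time of the draw". Section {17a} plans blinding for the data analysts only.

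**The concern.** Only treatment-arm women and their dependents use the reception, because controls are offered insurance only after data collection ends. Contact with project enumerators as helpers is therefore specific to one arm, and so is an in-interview discussion of what went wrong at the hospital. Gratitude, courtesy, annoyance or priming can then move answers in the treatment arm without any change in health or behaviour.

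The exposed measures are the self-reported STI symptoms, which the protocol lists within its primary outcome, and most secondary outcomes: general health, violence, stress, stigma, mental health and income. The planned mediation analysis through risky sexual behaviours also draws on interview answers. Analyst blinding does not help, because the difference is already in the data.

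**Working it through.** **Step 1: do the documents support the two routes?**

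- *Shared role.* {11a} gives the reception enumerator a part in the ODK-based survey, {19} has enumerators administer the socioeconomic questionnaires, and {33} calls the 0, 6 and 12 month socioeconomic survey ODK-based. ODK forms also record consent ({26a}) and the draw ({16c}), but the outcome survey is the natural reading of {11a}. No section separates hospital duty from interview duty.
- *Discussion in the interview.* {11c} places it during the survey. This departs from the rest of {11c}, which puts reminders and resolution at the end.

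**Step 2: which outcomes can be affected?**

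| Outcome | Open to this bias? |
|---|---|
| Tested HIV and STIs | No |
| STI symptoms, last 30 days | Yes |
| Condom use | Partly protected (double list experiment, colourbox method) |
| Measures taken by SMS | No interviewer involved |
| Other interview-based secondary outcomes | Yes |
| Patient satisfaction | Implementation indicator; no comparison between arms is described |

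**Step 3: illustration of size.** The protocol gives no figure for reporting bias, so there is none to reproduce. Inputs: 568 control and 579 treatment participants (Sample size {14}). Assumptions: a two-sided 5% test, a yes/no item at 50% or 30% in both arms, no true effect, and a reporting shift d averaged over the whole treatment arm.

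The pooled test rejects when the observed difference exceeds 1.96 × SE0, where SE0 = √[p̄(1 − p̄)(1/568 + 1/579)]. With SE1 = √[pC(1 − pC)/568 + pT(1 − pT)/579], the rejection probability is

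1 − Φ[(1.96·SE0 − d)/SE1] + Φ[(−1.96·SE0 − d)/SE1].

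For pC = 0.50 and pT = 0.53: p̄ = 0.5151, SE0 = 0.02951, SE1 = 0.02950 and 1.96·SE0 = 0.05785. The first term is 1 − Φ(0.944) = 0.173 and the second is Φ(−2.978) = 0.001, giving 0.174 from unrounded terms.

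| Item | d = 0 | d = 3 points | d = 5 points |
|---|---|---|---|
| 50%, either direction | 5% | 17% | 40% |
| 30%, shift upward | 5% | 19% | 44% |
| 30%, shift downward | 5% | 20% | 47% |

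**Step 4: dilution.** Only exposed women contribute: those interviewed by an enumerator with hospital duty after using the hospital, and those whose bad experience is discussed in the interview. Arm shift = exposed fraction × shift among the exposed. If 30% were exposed (assumed), a 3-point arm shift needs 3/0.30 = 10 points among them, and 5 points needs 5/0.30 = 16.7. At 50% exposed the figures are 6 and 10 points. Conversely, a 5-point shift among 30% exposed is 0.30 × 5 = 1.5 points over the arm, and the false-positive rate is then 8% (50% item) or 9% (30% item).

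**The case against.** The best defence has five parts.

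1. **Dual role is not proof of contact.** A reader might infer that treated women were interviewed by the very person who arranged their care. No section says so. Hospital enumerators are based at the hospital, while {27} places the surveys in private rooms at the community organisations. This stands as a limit on what can be claimed. Separation by place is still not a rule on who interviews, so the risk remains.
2. **{11c} already puts resolution last.** A reader might infer that all insurance problem-solving happens inside the interview. It does not. Only discussion of a bad experience is placed there, and only for women who report one. The point is confined to that sentence.
3. **Question order is not shown.** The questionnaire is not in the protocol, so it cannot be said that insurance questions precede outcome questions. This stands.
4. **Timing.** Cover ended on 14 November 2022 and this version is dated 10 March 2023, with follow-up continuing. Staffing and ordering rules can reach only the interviews that remain, which may be few. This stands, and it gives the analysis of completed interviews more weight.
5. **Participants cannot be blinded.** Some reporting bias would remain under any staffing. True, but the overlap of roles and the mid-interview discussion are the avoidable part. The reason {17a} gives for leaving researchers unblinded does not require either.

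**Conclusion.** The point holds in limited form. As written, the plan adds two avoidable influences, in the treatment arm only, on self-reports collected by interviewers. It is worth correcting, but it does not threaten the tested STI and HIV results, on whose incidence the sample size rests. A reader might extend the concern to those results, but nothing in the text supports that.

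Size and direction are unknown. The bias could create a difference or hide one, since helper contact and complaints may pull answers in opposite directions. The 17% to 44% false-positive range (47% for a downward shift at a 30% item) should not be read as a forecast. It rests on an assumed 3 to 5 point shift averaged over the whole arm, which requires a much larger shift among the women actually exposed. The Discussion itself anticipates under-use of care, which would keep that group small.

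**What to change.** 1. **{11c}:** replace the sentence "This problem will be discussed whilst the participant is being surveyed by the enumerator" so that the interviewer only records a bad experience, and all discussion takes place with the site supervisor at the end of the survey, where {11c} already puts resolution.
2. **{11c} and {18a}, any remaining interviews, both arms:** state that enumerators with hospital-reception duty do not administer the outcome survey. Ask the insurance-experience questions after the outcome questions, if they are not already last.
3. **{20b}, completed interviews:** where enumerator identity was recorded (the protocol does not say whether it was), repeat the self-report comparisons without interviews by hospital-duty enumerators, excluded in both arms, as a sensitivity analysis.

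The cost is a rota rule, an edit to the interview procedure and one extra analysis. The downsides are less flexible scheduling, a possible difference in question order between survey rounds, and some loss of precision in the sensitivity analysis.
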